**6.1.2.6 Sequence and duration of all study periods**

See Randomized controlled trial flowchart below. Study inclusion is planned over 18 months.

See also chapter 9.1 Study flow chart / Table of study procedures and assessments.

[figure not shown]

**6.1.3 Mechanisms analysis (Aim 3)**

Participants will be asked for additional consent to audio-record intervention sessions. Then, audio-recorded sessions will be analysed using psycholinguistic coding.

In addition, a random sub-sample of 20 BA and 20 BMI sessions will be transcribed and analyzed using thematic analysis and recursive abstraction techniques (Maxwell, 2005).

Also, semi-structured interviews will be conducted after the 1-month and 12-month follow-up questionnaire with another randomly selected 10 patients having received BA and 10 MI sessions. Topics addressed will be qualitative assessment of potential short-/long-term changes experienced during the follow-up period and their relation or not with the intervention received.

## **6.2 Methods of minimising bias**

### **6.2.1 Randomisation**

Randomization will be performed using an algorithm implemented in the same software used to collect baseline assessment (secuTrial). The unit will be the participants and there will be no stratification. There will be the exact same chance for each participant to receive intervention a) or b).

The algorithm will be developed and implemented by the Lausanne Clinical Trial Unit and will thus be totally independent of the research field staff and research investigators.

### **6.2.2 Blinding procedures**

Participants will be blinded to which kind of interventions they are receiving. Both interventions will be presented as “clinical interviews”. They might realize that they had received a more or less long or intense intervention.

Clinicians cannot be blinded to the type of intervention they will have to deliver.

ER staff and related care providers will be blinded to intervention allocation. They will only know that the participant has received a secondary prevention intervention relative to alcohol use and consequences. They will provide care as usual to all participants.

Follow-up interviews will be conducted by research assistants, specifically trained for the research project, not implicated in baseline procedures, and blinded to patients’ group allocation and prior data. Weekly supervision will be organized with the PI to ensure data collection quality.

Data analysts will not be blinded.

### **6.2.3 Other methods of minimising bias**

All questionnaires and randomization will be conducted and recorded on a secured electronic case report form (eCRF) managed by the Clinical Trial Unit, Lausanne, warranting data integrity, security, quality and traceability.

Weekly supervision will be organized with the PI to ensure data collection quality. Additional clinical supervision will be ongoing with [name] to answer any clinical challenges encountered with study patients.

## **6.3 Unblinding Procedures (Code break)**

Not applicable

## 7. STUDY POPULATION

### 7.1 Eligibility criteria

Participants fulfilling all of the following inclusion criteria are eligible for the study:

- a) between the age of 18 and 35
- b) admitted in the Lausanne University Hospital ER (for any cause) and having alcohol intoxication (>0.5 gram/liter BAC or clinical indication of alcohol intoxication)
- c) Informed consent as documented by signature (see Appendix Informed Consent Form)

The presence of any one of the following exclusion criteria will lead to exclusion of the participant:

- a) life threatening conditions;
- b) detainees or medico-legal admissions;
- c) not being fluent in French;
- d) currently receiving another alcohol or substance use treatment;
- e) psychiatric or medical contra-indications preventing patients understanding informed consent, fulfilling questionnaires, and participating in the intervention (evaluated using an adaptation of the University of California, San Diego Brief Assessment of Capacity to Consent; McCormack et al. 2014).

### 7.2 Recruitment and screening

The study will be conducted at the Lausanne University Hospital ER, Switzerland. According to administrative data over 7 weeks randomly selected between November 2012 and March 2013, intoxicated young adults are admitted almost only in the later part of the week. For economic reasons, we will limit study recruitment in the ER to Thursday to Sunday mornings from 7am to 2pm, covering 85% of eligible patients. Patients meeting inclusion criterion and having been treated outside this time frame will be contacted by phone and proposed to come to Lausanne University Hospital Alcohol Treatment Center to participate in the study.

All consecutive patients between the age of 18 and 35, admitted in the ER (for any cause) and having alcohol intoxication (>0.5 gram/liter BAC or clinical indication of alcohol intoxication) will be contacted by a member of the research staff during study period. Patients meeting inclusion criterion but being too intoxicated will be contacted by research staff once they have sobered up.

First, research staff will conduct a screening process to evaluate inclusion and exclusion criterion (see Chapter 7.1 above). In case only exclusion criteria e) is not fulfilled (i.e. psychiatric or medical contra-indications preventing patients understanding informed consent, fulfilling questionnaires, and participating in the intervention; evaluated using an adaptation of the University of California, San Diego Brief Assessment of Capacity to Consent – UBACC; McCormack et al. 2014), research staff will come back later to re-assess UBACC and complete further study process if the UBACC score is positive.

For those included, baseline assessment questionnaire will then be conducted in the ER, in a separate space providing confidentiality and using a tablet-based electronic questionnaire administered by a research clinician. The questionnaire will be short (about 5 minutes), first as patients might be hung-over as a result of alcohol intoxication, and second to reduce reactivity to alcohol assessment which has been shown as a source of bias (Gallen, 1974; McCambridge & Kypri, 2011).

### 7.3 Assignment to study groups

After completing the computer-based assessment, the software will automatically randomize participants into 2 equivalent groups: a) Brief motivational intervention (experimental condition) and b) Brief advice (control condition).

### 7.4 Criteria for withdrawal / discontinuation of participants

Each participant will be informed that study participation is voluntary and he/she may withdraw from

the study at any time.

Participants will be considered included in the study when signing informed consent.

Participants withdrawing before starting interventions will be replaced to obtain sufficient power (N=344 participants having received intervention). Participants withdrawing after having started brief intervention (either experimental or control) will not be replaced.

Investigators will not withdraw included participants from the study.

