## **8.5 Data Collection and Follow-up for withdrawn participants**

Investigators will not withdraw participants from the study. Participants may withdraw from the study at any time and might be lost to follow-up.

Participants withdrawing from the trial will not be contacted for subsequent questionnaires. However, if they consented to within the initial consent process, their hospital administrative records will be consulted to have an objective, non self-report measure of readmission in the ER and alcohol treatment at 12 months post baseline.

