### **11.4 Planned Analyses**

#### **11.4.1 Datasets to be analysed, analysis populations**

Primary analyses of the efficacy of the intervention (randomized controlled trial) will use all data available from all participants included in the trial. Analysis will be performed in an intention to treat paradigm (i.e. participants having left the ER without finishing the intervention, and/or not receiving intervention booster sessions will be analyzed in the intervention group).

Secondary analysis of mechanisms (Aim 3 of the project) will use data available for the corresponding analyses (e.g. participants with audio-recorded sessions for psycholinguistic coding; randomly selected sub-sample for qualitative analyses). Also, moderation analyses are designed as part of the mechanism analyses. For these, the relative efficacy of the BMI will be tested as an interaction with participants' characteristics, such as age, gender, alcohol problems severity, readiness to change, or personality traits.

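### Section 7.4 replaces people already randomised and counts the 344 at session start, which does not fit the intention-to-treat analysis in 11.4.1

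*Protocol*

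**What the plan says.** Section 7.4 sets three rules.

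- Inclusion is at consent: "Participants will be considered included in the study when signing informed consent".
- Early leavers are replaced: "Participants withdrawing before starting interventions will be replaced to obtain sufficient power (N=344 participants having received intervention".
- Later leavers are not: "Participants withdrawing after having started brief intervention (either experimental or control) will not be replaced".

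Section 7.3 puts allocation before the session: "After completing the computer-based assessment, the software will automatically randomize participants into 2 equivalent groups". The Day 1 list in 9.3.1 gives the same order: consent, baseline questionnaire, randomisation, intervention.

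Section 11.2 sizes the trial at 344 participants, 172 per group, for an effect of 0.25 with power 0.8 and alpha 0.05. It already allows for 5-20% attrition over the follow-ups.

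Section 11.4.1 says that the primary analyses "will use all data available from all participants included in the trial" and adds: "Analysis will be performed in an intention to treat paradigm". It explains this by two cases: "participants having left the ER without finishing the intervention, and/or not receiving intervention booster sessions will be analyzed in the intervention group".

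Section 8.5 closes off later data: "Participants withdrawing from the trial will not be contacted for subsequent questionnaires". Section 9.2.5 repeats this. Only hospital records at 12 months remain, and only for those who consented to their use.

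**The concern.** The replacement rule is tied to the start of the session and not to randomisation. It therefore treats two different groups alike: people who leave between consent and randomisation, and people who leave after being allocated. Replacing the first group is harmless. Replacing the second turns the recruitment target into a count of people who began an intervention.

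The arms can differ at this step. The interventionists who recruit and assess patients also deliver both interventions (1.7.4.2), and they know the allocation (6.2.2). What follows is either about 5-10 minutes of brief advice or 20-60 minutes of motivational intervention (8.2.1, 8.2.2), with patients who may be hung-over (7.2). If those who leave differ in prognosis and leave one arm more often, a comparison of starters is no longer the randomised comparison that the plan promises.

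**Working it through.** **Step 1. What happens to each kind of leaver.**

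| Leaves the study | Replaced (7.4)? | Heavy drinking days and SIP (8.5, 9.2.5) | Place in 11.4.1 |
|---|---|---|---|
| After consent, before randomisation | Yes | None | Included under 7.4, but has no arm |
| After randomisation, before the session | Yes | None | Included under 7.4, but not named in the intention-to-treat explanation |
| After the session starts | No | Up to withdrawal | Named; analysed in the assigned group |

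The middle row is the problem. Such people are replaced and supply no primary outcome data. An all-available-data analysis then rests on starters, topped up to 344. Read literally, the 11.4.1 set is everyone who signed consent. Read through 7.4, it is everyone who started a session. Neither is everyone randomised.

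The choice also reaches a secondary outcome. Hospital-record outcomes are still collected for withdrawn participants who consented (5.2 f, 8.5), so counting never-starters in their arm or not can change that result.

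**Step 2. The plan's own 172 per group.** With z(0.975) + z(0.80) = 1.960 + 0.842 = 2.802 (two-sided alpha assumed), a single time point needs n = 2 × 2.802² / 0.25² = 251.2, so 252 per group. For three follow-ups, n = 2 × 2.802² / (0.25² × I). Here I is the expected information per person under correlation ρ^(lag^θ), with visits one unit apart and monotone dropout. The protocol gives no ρ or θ. Assuming ρ = 0.5, θ = 0.75 and retention of 95, 87.5 and 80%, n = 172. With that retention, ρ from 0.3 to 0.7 and θ from 0 to 1 give 136 to 216. The figure is attainable but cannot be reproduced from the stated inputs alone. It is a number of participants, not of intervention recipients.

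**Step 3. Possible bias.** Let w be the share lost from one arm only, and g the gap in SD between those lost and the starters in that arm. The starters' mean differs from the full-arm mean by w × g. The protocol gives neither value; both are assumed.

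- w = 2%, g = 0.5: 0.02 × 0.5 = 0.01 SD; 0.01 / 0.25 = 4% of the target effect
- w = 5%, g = 0.5: 0.05 × 0.5 = 0.025 SD; 10%
- w = 10%, g = 0.5: 0.10 × 0.5 = 0.05 SD; 20%

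**Step 4. Cost of not replacing.** Take 344 randomised, nominal power 80%, and an assumed never-starter share w.

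- No outcomes from never-starters: power = Φ(2.802 × √(1 − w) − 1.960)
- Never-starters followed, with zero effect: power = Φ(2.802 × (1 − w) − 1.960)
- Randomised number needed for 344 starters: 344 / (1 − w), rounded up

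| w | No outcomes | Followed, zero effect | Needed for 344 starters |
|---|---|---|---|
| 1% | 79.6% | 79.2% | 348 |
| 2% | 79.2% | 78.4% | 352 |
| 5% | 78.0% | 75.9% | 363 |
| 10% | 75.7% | 71.3% | 383 |

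At low rates the power reason for replacing allocated people is weak.

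**The case against.** The best defence is that replacement is a recruitment rule and excludes nobody. Section 7.4 counts people as included from consent and says that investigators will not withdraw them, and 11.4.1 takes everyone included. Someone who leaves before starting has also not finished, so the intention-to-treat wording can be stretched to cover them. This stands as far as it goes: no section removes never-starters, and recruiting extra people does not by itself breach intention to treat. It does not supply outcome data for them, however. Section 11.5 offers imputation only as something to explore if systematic missingness is found.

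Second, participants are blinded. The information sheet does not mention two groups (2.7), both interventions are presented in the same terms (6.2.2), and the length of the motivational session is negotiated once it is under way (3.5). Someone put off by its length would mostly find out after the start, when no replacement occurs and the assigned group is kept. The session is also the next Day 1 step after allocation. This weakens the case for differential refusal considerably. It does not rule it out, because the clinician knows the arm.

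Third, the data loss comes from the no-contact rule in 8.5 and 9.2.5 and not from replacement. That is correct, and it means that rewriting 7.4 alone would leave any bias in place.

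**Conclusion.** The inconsistency holds. As written, 7.4 replaces people already allocated and sets a target of session recipients. Combined with the no-contact rule, it makes the effective primary population those who started a session, under an intention-to-treat label and against a sample size stated as participants.

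A reader might go further and infer that the protocol discards randomised never-starters, breaks the randomisation and favours the motivational arm. The documents do not support that. No deletion is stated, participant blinding limits differential departure, and neither the number nor the prognosis of never-starters is given. Bias is possible, not shown. The 0.01-0.05 SD range (4-20% of the 0.25 target) rests on an assumed 2-10% loss confined to one arm and an assumed 0.5 SD gap. Equal loss of similar people from both arms would give little or none.

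**What to change.** - **7.4:** count the 344 at randomisation and replace only those who withdraw before it.
- **11.4.1:** define the primary set as all randomised participants, including those who never start a session, analysed in the assigned arm.
- **8.5 and 9.2.5:** state that declining or leaving before the session is not withdrawal from follow-up unless the participant refuses further contact.
- **Reporting:** give never-starters by arm. An analysis of those who started may be kept as a sensitivity analysis.

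Use of any participant's data would remain subject to the end-of-follow-up consent in 2.7.

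The cost is a short amendment, which probably needs ethics committee approval under 2.3 and 2.10, and a slight loss of power or dilution of the effect. With an assumed 1-5% of never-starters, the loss from a nominal 80% is about 0.4-2 points if they give no outcomes, or about 1-4 points if they are followed and show no effect. If that matters, the number randomised can be raised without redefining the target population.

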## **8. STUDY INTERVENTION**

### **8.1 Identity of Investigational Products (treatment / medical device)**

#### **8.1.1 Experimental Intervention (treatment / medical device)**

The experimental treatment will be the brief motivational intervention (BMI) developed and pre-tested in the first phase of the project.

#### **8.1.2 Control Intervention (standard/routine/comparator treatment / medical device)**

The control intervention will be a minimal intervention - *Brief advice*.

#### **8.1.3 Packaging, Labelling and Supply (re-supply)**

Not applicable.

#### **8.1.4 Storage Conditions**

Not applicable.

### **8.2 Administration of experimental and control interventions**

#### **8.2.1 Experimental Intervention**

BMI will be delivered while in the ER by a qualified research clinician (psychologist, clinical social worker, or nurse) and will last between 20 to 60 minutes.

The intervention will use 3 main ingredients, in particular a) relational factors (e.g., empathy, acceptance, collaboration, avoidance of confrontation), b) evoking participants' change talk and strengthening their ability and commitment to change, and c) build a relationship significant in the long-run (e.g., including follow-up booster sessions). Overall, the intervention aims at increasing participants' motivation to change their drinking behaviours by enhancing discrepancy between their current behaviour and their broader life goals and values. The intervention focuses on helping participants to resolve the latter discrepancy through evoking and planning behaviour change. When necessary, interventionist will discuss and facilitate referral to alcohol treatment.

After the session, the interventionist sends a letter summing up the discussion (i.e., context, discussion, aims and encouragements) to the participant. Based on participant's agreement, booster session by phone will be conducted after 2 weeks, 1 month, and 3 months.

#### **8.2.2 Control Intervention**

The control intervention will be a minimal intervention - *Brief advice (BA)* - delivered in approximately 5 to 10 minutes while in the ER by the same qualified research clinicians (psychologist, clinical social worker, or nurse). It will consist of a standardized computer-based brief structured feedback and advice to cut down drinking, with referral to specialist services for the more severe patients (based on the Alcohol Use Disorders Identification Test score included in the baseline assessment).

### **8.3 Dose / Device modifications**

Not applicable.

### **8.4 Compliance with study intervention**

Interventionists will be clinicians experienced in counseling and liaison for alcohol use disorder (psychologists, clinical social workers, or nurses). They will not be ER staff; firstly to avoid additional workload for the ER staff; and secondly as recent research showed that liaison consults and

interventions delivered by addiction specialists were more appropriate and effective (Schwan et al. 2012; Dunn et al. 2014).

Clinicians will be selected to have at least 1 year experience with alcohol use disorder and MI, as experienced therapists and MI skills have been shown as important predictors of better alcohol BMI outcomes (Gaume et al. 2009; Gaume et al. 2014a, Gaume et al. 2016). They will be specifically trained to provide the present intervention. Proficiency in MI will be assessed during training MI sessions with standardized patients, coded using the MI Treatment Integrity coding scheme (MITI; Moyers et al. 2005a).

Ongoing supervision will be provided throughout the project with interventions reviewed by a senior clinician expert in MI and feedback given to the clinician during biweekly supervision meetings.

BMI integrity will be assessed by the supervisor using the MITI. Adherence to the BA model and to the new BMI model will be assessed using an ad-hoc Components Inventory developed for this project after Phase 1. This instrument will be developed similar to the Process Rating Scale (Tober et al. 2008) used in the United Kingdom Alcohol Treatment Trial (UKATT, i.e. a check list of intervention components with 2 items by component: a) the extent to which the component was performed, and b) the quality of this performance). Interventionists performing interventions under acceptable thresholds will be notified during the next supervision, and will be replaced if practice is judged consistently below the identified levels over time.

## **8.5 Data Collection and Follow-up for withdrawn participants**

Investigators will not withdraw participants from the study. Participants may withdraw from the study at any time and might be lost to follow-up.

Participants withdrawing from the trial will not be contacted for subsequent questionnaires. However, if they consented to within the initial consent process, their hospital administrative records will be consulted to have an objective, non self-report measure of readmission in the ER and alcohol treatment at 12 months post baseline.

## **8.6 Trial specific preventive measures**

Not applicable.

## **8.7 Concomitant Interventions (treatments)**

Not applicable.

## **8.8 Study Drug / Medical Device Accountability**

Not applicable.

## **8.9 Return or Destruction of Study Drug / Medical Device**

Not applicable.

## 9. STUDY ASSESSMENTS

### 9.1 Study flow chart(s) / table of study procedures and assessments

| Phase 1 – Development (N=12)                                                                                                                                                                                                                     |                    |                        |                   |           |       |                                 |   |                            |   |
|--------------------------------------------------------------------------------------------------------------------------------------------------------------------------------------------------------------------------------------------------|--------------------|------------------------|-------------------|-----------|-------|---------------------------------|---|----------------------------|---|
| Visit                                                                                                                                                                                                                                            |                    |                        |                   |           |       |                                 |   | 1 (in the ER)              |   |
| Patient Information and Informed Consent                                                                                                                                                                                                         |                    |                        |                   |           |       |                                 |   | x                          |   |
| Brief motivational intervention with research clinician                                                                                                                                                                                          |                    |                        |                   |           |       |                                 |   | x                          |   |
| Qualitative interview with research collaborator                                                                                                                                                                                                 |                    |                        |                   |           |       |                                 |   | x                          |   |
| Phase 2 – Randomized controlled trial (N=342)                                                                                                                                                                                                    |                    |                        |                   |           |       |                                 |   |                            |   |
| Study Periods                                                                                                                                                                                                                                    | Baseline procedure | Intervention           | Post-intervention | Follow-up |       |                                 |   |                            |   |
| Time (months)                                                                                                                                                                                                                                    | 0                  |                        |                   | 1         | 3     | 6                               |   | 12                         |   |
| Visit                                                                                                                                                                                                                                            | 1                  |                        |                   | 2         | 3     | 4                               | 5 | 6                          | 7 |
| Location (ER=Emergency Room, T=telephone, A=Alcohol Treatment Center)                                                                                                                                                                            | ER                 |                        |                   | T         | T     | T                               | A | T                          | A |
| Expected duration (minutes)                                                                                                                                                                                                                      | 15                 | BMI: 20-60
BA: 5-10 | 5                 | 15-20     | 20-30 | 20-30                           | 5 | 15-20                      | 5 |
| In- /Exclusion Criteria                                                                                                                                                                                                                          | x                  |                        |                   |           |       |                                 |   |                            |   |
| Patient Information and Informed Consent                                                                                                                                                                                                         | x                  |                        |                   |           |       |                                 |   |                            |   |
| Demographics (questionnaire)                                                                                                                                                                                                                     | x                  |                        |                   |           |       |                                 |   |                            |   |
| Primary outcomes variables (questionnaires)                                                                                                                                                                                                      | x                  |                        |                   | x         | x     | x                               |   | x                          |   |
| Secondary outcomes variables (questionnaires)                                                                                                                                                                                                    | x                  |                        |                   | x         | x     | x                               |   | x                          |   |
| Other outcomes of interest (questionnaires)                                                                                                                                                                                                      | x                  |                        | x                 | x         | x     | x                               |   |                            |   |
| Randomisation                                                                                                                                                                                                                                    | x                  | x                      |                   |           |       |                                 |   |                            |   |
| Intervention with research clinician:                                                                                                                                                                                                            |                    | x                      |                   |           |       |                                 |   |                            |   |
| Head hair sample (only if hair>2 cm and additional consent)                                                                                                                                                                                      |                    |                        | x                 |           |       |                                 | x |                            | x |
| Consultation of administrative and medical records (only if additional consent)                                                                                                                                                                  |                    |                        |                   |           |       |                                 |   | Not in presence of patient |   |
| Phase 3 – Mechanisms analysis                                                                                                                                                                                                                    |                    |                        |                   |           |       |                                 |   |                            |   |
|                                                                                                                                                                                                                                                  |                    |                        |                   |           |       | Timing                          |   |                            |   |
| 15-20 minute qualitative semi-structured interview after follow-up questionnaire (N=10 participants in BMI and 10 in BA groups, randomly selected and consenting to continue the follow-up questionnaire with a discussion on their experience). |                    |                        |                   |           |       | At the end of 1-month follow-up |   |                            |   |

|                                                                                                                                                                                                                                                  |                                              |
|--------------------------------------------------------------------------------------------------------------------------------------------------------------------------------------------------------------------------------------------------|----------------------------------------------|
| 15-20 minute qualitative semi-structured interview after follow-up questionnaire (N=10 participants in BMI and 10 in BA groups, randomly selected and consenting to continue the follow-up questionnaire with a discussion on their experience). | At the end of 12-month follow-up             |
| Psycholinguistic coding of audio-recorded interventions (N=all interventions with patient's consent for audio-recording and no technical problems)                                                                                               | End of inclusion, not in presence of patient |
| Qualitative analysis of transcribed intervention sessions (N=10 BMI and 10 BA, randomly selected among all interventions with patient's consent for audio-recording and no technical problems)                                                   | End of inclusion, not in presence of patient |

